#### Qualitative substudy

Within the feasibility study, a qualitative substudy will assess patient experience of having an open fracture of the lower limb, being enrolled in the study, giving or declining consent for the trial, and the acceptability of the trial procedures.

The sample will include patients at two UK sites (Coventry and Oxford). This will include standard wound care and negative pressure wound therapy. Semistructured interviews will be undertaken with up to 20 consecutive patients who provide informed consent for the interview during their hospital stay. Participants will be given information about the interview study and provide written consent. The interviews will be conversational in style^19^ and focus on three areas (1) the experience of open fracture of the lower limb, (2) the impact and acceptability of the trial procedures, and (3) the process of consent to a trial. Those who preferred not to take part in the trial will be asked to tell us about (1) the experience of open fracture of the lower limb, and (2) their thoughts and feelings about the trial. The key interview questions will be what is it like: to experience an open fracture; have an open wound and dressing/negative pressure wound therapy; to be part of a trial/prefer not to take part in a trial? These will be followed by prompts such as: tell me more about that; how did that affect you; how did you feel about that; what were you thinking at that point. The interviews will take place in hospital when the patients are well enough and feel able to take part in the interview. Where possible, these interviews would take place in a private area on the ward, but at the bedside is more likely due to the nature of the injury. Attention will be paid to privacy and dignity of the patient, and the interview will be stopped and reconvened if the patient is uncomfortable or feels that their privacy is being compromised.

Interviews will be performed with both patients who agree to continue in the trial and those who decline to be further involved. The research team is aware that ethically patients do not have to provide a reason for their choice and should not be coerced in anyway. However, in light of the limited knowledge in this area, the value of understanding what trauma patients’ think and feel about research in this context would be substantial and would help to inform the recruitment process in the main trial. The researcher would take an exploratory, non-judgemental stance while allowing the patient to tell their story. As interviews will take place with participant refusers after they have withdrawn from the trial, the interview cannot be construed as coercive in relation to the trial.

Two focus groups, 1 on each site with up to 12 staff, will be undertaken with staff involved in the management of the trial or the management of patients in the trial. This will include surgeons, emergency department staff, theatre staff, ward staff and research staff. The participants will consider the factors that facilitate and inhibit the daily process of running the trial. This will include optimal timing and method to approach the patient with the participant information. Focus groups are a good way to access a range of views on a topic and provide opportunities for debate and challenge within the group.^20^ Managing the dynamics of a group is important to ensure all participants have a chance to share their views and strong views are contained. Attention will be paid to this through the use of basic ground rules and good facilitation of the group. The focus group discussions will take place in a quiet room away from interruptions. The interviews and focus groups’ meetings will be digitally recorded and transcribed verbatim. Analysis will be line-by-line, identifying codes, building categories and themes by drawing on the work of Miles and Huberman.^21^ NVivo9, a software package for qualitative data, will be used to help with data management. The intention of the patient interviews is to understand how patients make sense of their treatment and to specifically address any issues related to their consent to participate. The focus groups will develop a greater understanding of the factors that facilitate and inhibit the process of the trial. The qualitative data will be used to provide indepth understanding of the process to augment the quantitative data.

#### Trial ID

When a patient enters the trial, sufficient non-identifiable details will be logged on a secure, encrypted, web-based system, provided by York CTU. Basic information, including the patient's initials, date of birth, gender and eligibility checks will be entered. The patient will then receive a trial ID that will be used on all trial documentation.

#### Randomisation

The allocation sequence will be generated by an independent randomisation centre—York CTU. Randomisation will be on a 1:1 basis, stratified by trial centre and Gustilo and Anderson grade—2, 3, or 3 with vascular injury requiring surgical repair. Eligibility for the trial is based on a wound of grade 2 or above, which will be established definitively at the end of the initial surgical debridement in the operating theatre as per routine clinical practice. Therefore, participants will be assigned to their treatment allocation at the end of the initial surgery, but before the wound dressing is applied. All modern operating theatres include a computer with web-access; so a secure, 24 h, web-based randomisation system will be used to generate the treatment allocation intraoperatively.

#### Post randomisation withdrawals/exclusions

Participants will be excluded in the postrandomisation phase if it is established that they would be unable to adhere to trial procedures or complete questionnaires.

Participants may decline to continue to take part in the trial at any time without prejudice. A decision to decline consent or withdraw will not affect the standard of care the patient receives.

Participants have three options for withdrawal:
Participants may withdraw from completing any further questionnaires, but allow the trial team to still view and record anonymously any relevant hospital data that is recorded as part of normal standard of care, that is, X-rays and further surgery information.Participants can withdraw wholly from the study, but data obtained up to the point of withdrawal will be included in the final analysis of the study; thereafter, no further data will be collected for that participant.Participants can withdraw wholly from the study and data collected up to the point of withdrawal will not be included in the final analysis.

Once withdrawn from the study, the patient will be advised to discuss their further care plan with their surgeon.

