### Methodology

#### Eligibility

Patients will be eligible for this study if:
They are aged 16 years or olderPresent to the trial hospital within 72 h of injuryHave an open fracture of the lower limb—graded as Gustilo and Anderson 2 or 3.

Patients will be included if they are transferred from another hospital to a trial centre within 72 h of their injury. (A very small number of patients may present after 72 h, but there is a possibility that any wound would already be infected with later presentations).

Patients will be excluded from participation in this study if:
There are contra-indications to anaesthesia such that the patient is unable to have surgeryThere is evidence that the patient would be unable to adhere to trial procedures or complete questionnaires, such as permanent cognitive impairment. It is expected that for a very small proportion of patients this exclusion criterion will only be determined after randomisation has taken place. These patients will then be excluded from the study and no patient identifiable data will be retained.

Patients who sustain other injuries which may affect the primary outcome measure will have their injuries documented, but will be included in the analysis.

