#### Blinding

As the wound dressings are clearly visible, the patients cannot be blinded to their treatment. In addition, the treating surgeons will also not be blind to the treatment, but will take no part in the postoperative assessment of the patients. The functional outcome data will be collected and entered onto the trial central database via postal questionnaire by a research assistant/data clerk in the trial central office.

In addition, we will use photographs of the wound at the 6-week clinical follow-up to provide an objective assessment of wound healing and infection. The photographs will be reviewed independently by two experienced assessors who are blind to the treatment allocation.

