### Main RCT

Standard statistical summaries (eg, medians and ranges or means and variances dependent on the distribution of the outcome) and graphical plots showing correlations will be presented for the primary outcome measure and all secondary outcome measures. Baseline data will be summarised to check comparability between treatment arms, and to highlight any characteristic differences between those individuals in the study, those ineligible and those eligible, but withholding consent.

The main analysis will investigate differences in the primary outcome measure, the DRI score at 1 year after injury, between the two treatment groups (standard wound dressings and negative pressure wound therapy) on an intention-to-treat basis. In addition, early functional status will also be assessed and reported at 3, 6 and 9 months. Differences between groups will be assessed, based on a normal approximation for the DRI score at 12 months postinjury and at interim occasions. Tests will be two sided and considered to provide evidence for a significant difference if p values are less than 0.05 (5% significance level).

The stratified randomisation procedure should ensure a balance in Gustilo and Anderson grade and the recruiting centre's between-test treatments. Although generally we have no reason to expect that clustering effects will be important for this study, in reality, the data will be hierarchical in nature, with patients naturally clustered into groups by the recruiting centre. Therefore, we will account for this by generalising the conventional linear (fixed effects) regression approach to a mixed effects modelling approach, where patients are naturally grouped by recruiting centres (random effects). This model will formally incorporate terms that allow for possible heterogeneity in responses for patients due to the recruiting centre, in addition to the fixed effects of the treatment groups, Gustilo and Anderson grade, and other patient characteristics that may prove to be important moderators of the treatment effect such as age and gender.

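### Randomised patients can be excluded after allocation on a judgement not tied to pre-randomisation facts or kept blind to arm, although the main analysis is called intention-to-treat

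*Protocol article*

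**What the plan says.** Two sections of the protocol article set the rule.

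- The section on withdrawals and exclusions after randomisation states: "Participants will be excluded in the postrandomisation phase if it is established that they would be unable to adhere to trial procedures". The same sentence extends this to patients who could not fill in the questionnaires.
- Eligibility lists the same inability as an exclusion criterion, gives permanent cognitive impairment as an example, and adds: "It is expected that for a very small proportion of patients this exclusion criterion will only be determined after randomisation has taken place". It continues: "These patients will then be excluded from the study and no patient identifiable data will be retained".

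The Main RCT part of the Statistical analysis section compares the 12-month DRI "between the two treatment groups (standard wound dressings and negative pressure wound therapy) on an intention-to-treat basis", and the Abstract says the same.

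On timing and masking, the Randomisation section says that "participants will be assigned to their treatment allocation at the end of the initial surgery, but before the wound dressing is applied". The Blinding section says: "As the wound dressings are clearly visible, the patients cannot be blinded to their treatment". It adds that the treating surgeons are not blind either, but do not take part in postoperative assessment. The protocol does not say who decides on a late exclusion, or by when.

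**The concern.** An intention-to-treat comparison keeps every randomised patient in the arm to which he or she was allocated. Here a patient can leave the study after allocation because someone judges that he or she could not comply or respond. If that judgement draws on events after the dressing was applied, it can depend on the arm, and the remaining groups are then no longer those formed by randomisation.

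Two things are at stake. The first is the DRI comparison, if exclusion rates differ between arms and excluded patients would have scored differently. The second is outcomes that do not need the patient to answer anything: deep infection, further operations and radiographs. These could still be taken from hospital records, but they are lost once the patient is excluded from the study.

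**Working it through.** **Does the text confine the rule to baseline ineligibility?**

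1. Eligibility treats the rule as a criterion recognised late, which points to a pre-existing condition. Cognitive impairment is only an example, however, and the section on post-randomisation exclusions repeats the rule without it.
2. Neither section sets a time limit, restricts the evidence to what was true before randomisation, or requires a decision without reference to allocation.
3. Allocation is made in theatre. Under Recruitment and consenting, most patients lack capacity at that stage and are approached after surgery. The second feasibility objective foresees checking capacity six weeks after injury. The judgement can therefore follow treatment and early complications.
4. Under Treatment options, later dressings follow the allocated treatment until the wound is closed. If trial procedures include this, the adherence part of the rule can depend on the arm.
5. The Main RCT section plans to summarise non-compliance and perhaps to model protocol violation as a response. That presumes that non-compliant patients are still in the data.

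So the text allows a reading on which the rule and the intention-to-treat label conflict, and nothing in it closes off that reading.

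**The plan's own figure.** Inputs from the Sample size section: difference 8, SD 25, two-sided 5%, power 90%.

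- Per arm: 2 × (1.960 + 1.282)² × 25² / 8² = 205.2, rounded up to 206, so 412 in total, as stated.
- With 10% loss: 412 / 0.90 = 457.8, so 458 against the stated 460.
- 460 × 0.90 = 414 evaluable, or 207 per arm, with power 90.2%.
- If late exclusions came on top of that loss, power would be 90.0% at 1% excluded and 89.7% at 2%. Power is hardly affected.

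**Possible bias in the DRI.** The protocol gives neither an exclusion rate nor a DRI gap, so both are assumed. Let e₁ and e₂ be the proportions excluded in the two arms, and D the gap in mean DRI between excluded and retained patients. With no true effect, each retained mean is shifted by e × D from the full mean, so

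bias = (e₂ − e₁) × D

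SE = 25 × √(1/(207(1 − e₁)) + 1/(207(1 − e₂)))

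type I error = P(|Z + bias/SE| > 1.96)

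For 1% v 3%: SE = 25 × √(1/204.9 + 1/200.8) = 2.48. With D = 10 the bias is 0.02 × 10 = 0.2. With D = 30 it is 0.02 × 30 = 0.6.

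| Excluded (assumed) | Bias, D = 10 to 30 | Share of the 8 points | Type I error |
|---|---|---|---|
| 2% v 2% | 0 | 0% | 5.0% |
| 1% v 3% | 0.2 to 0.6 | 2.5% to 7.5% | 5.1% to 5.7% |
| 0% v 5% (stress case) | 0.5 to 1.5 | 6.2% to 18.8% | 5.5% to 9.3% |
| 0% v 10% (stress case) | 1.0 to 3.0 | 12.5% to 37.5% | 6.8% to 22.1% |

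The last two rows go beyond what the protocol expects and show only how the formula behaves.

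**The case against.** The best defence is that both sections describe one eligibility criterion that is discovered late. That would be a natural result of randomising in theatre patients who mostly lack capacity. Removing patients for a fact fixed before randomisation, judged without reference to the arm, does not bias the comparison. This reading is plausible, but the wording does not secure it.

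It can also be said that surgeons apply the dressings, so keeping to them is not something the patient does. That weakens the adherence argument without removing it, because the protocol does not define which procedures count.

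The DRI is self-administered, so a patient who cannot answer has no score whether excluded or retained. This stands. Retention turns a hidden exclusion into a visible missing value and does not recover the score.

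Analysis sets are usually defined in the statistical analysis plan, which the protocol promises and which is not shown. But this is a rule of conduct: an analysis plan cannot bring back outcomes that were not collected after a patient was excluded.

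A reader might infer more than the text supports:

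- That the damage is beyond repair. Only identifiable data are barred from retention. The Trial ID section describes non-identifiable details logged at entry, and nothing says that the randomisation record is destroyed.
- That those who decide on exclusion know the allocation. The protocol neither says so nor prevents it.
- That the rule contradicts the statement that "Patients who sustain other injuries which may affect the primary outcome measure will have their injuries documented, but will be included in the analysis". Having injuries that affect the DRI is not the same as being unable to complete it.
- That patients who decline to continue will be compared only as a pooled group. The Main RCT section does not say this.

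**Conclusion.** The point holds as a defect of wording that bears on the primary comparison. The rule allows exclusion after allocation on grounds that may arise after allocation, and this does not fit the intention-to-treat label. The main exposure is through the adherence part of the rule and through lost hospital-record outcomes.

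The expected effect on the DRI is small: about 0.2 to 0.6 points against a target difference of 8, with type I error of 5.1% to 5.7%, and none if like patients are excluded equally. This rests on an assumed 1% v 3% exclusion and an assumed gap of 10 to 30 points. It also treats excluded patients as having a DRI that could have been observed, which is not so for those unable to answer.

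A reader might infer from the stress cases that the trial's error rate is seriously inflated. The protocol does not support that. A gap of 10 percentage points between arms needs at least 10% excluded in one arm, which is hard to square with the very small proportion expected.

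**What to change.** Reword the Eligibility and Post randomisation withdrawals/exclusions sections together:

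1. The only exclusion allowed after randomisation is ineligibility that already existed before it, judged from pre-randomisation information and without reference to allocation.
2. All other randomised patients stay, subject to consent, in the allocated arm. Missing DRI scores go through the missing-data approach already described in the Main RCT section. Outcomes available from hospital records are kept. The first withdrawal option already allows questionnaires to stop while hospital data continue.
3. The non-identifiable randomisation record is kept for every patient. Exclusions, with reasons, and declined continuation are reported by allocated arm.

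The cost is a wording change and a check on a very small number of patients. The downside is a few more missing DRI values, which retention makes visible but does not recover.

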#### Blinding

As the wound dressings are clearly visible, the patients cannot be blinded to their treatment. In addition, the treating surgeons will also not be blind to the treatment, but will take no part in the postoperative assessment of the patients. The functional outcome data will be collected and entered onto the trial central database via postal questionnaire by a research assistant/data clerk in the trial central office.

In addition, we will use photographs of the wound at the 6-week clinical follow-up to provide an objective assessment of wound healing and infection. The photographs will be reviewed independently by two experienced assessors who are blind to the treatment allocation.

### Trial treatments

Patients with an open fracture of the lower limb usually have surgery on the next available trauma operating list. Some patients may be transferred to a Major Trauma Centre for definitive care—within the first 48 h of injury—but will still have their initial surgery as soon as possible. All patients will receive a general or regional anaesthetic. The wound associated with the fracture is ‘debrided’ (surgical decontamination and cleansed) in the operating theatre and the fracture is treated with either internal or external fixation. At the end of the initial operation, a dressing is applied to the wound. This trial will compare two types of wound dressings: standard dressing versus negative pressure wound therapy.

#### Treatment options

Standard dressing: The standard dressing for open fractures comprises a non-adhesive layer applied directly to the wound which is covered by a sealed dressing or bandage. The standard dressing does not use ‘negative pressure’. The exact details of the materials used will be left to the discretion of the treating surgeon as per their routine practice, but the details of each dressing applied in the trial will be recorded.

NPWT: The NPWT dressing uses an ‘open-cell’, solid foam which is laid onto the wound followed by an adherent, sealed dressing. A hole is cut in the layer over the foam and a sealed tube is used to connect the foam to a pump which creates a partial vacuum over the wound. The basic features of the NPWT are universal, but the exact details of the dressing will be left to the discretion of the treating surgeon. Again, the details of the dressings used will be recorded in the trial documentation.

Both groups of patients will then follow the normal postoperative management of patients with an open fracture of the lower limb. This will usually involve a ‘second-look’ operation after 48 h, where a further debridement is performed and the wound closed (with sutures or a soft-tissue graft, as necessary). Depending on the specific injury and according to the treating surgeons’ normal practice, the wound may be redressed again pending further surgery. Any further wound dressing will follow the allocated treatment until definitive closure/cover of the wound is achieved.

#### Rehabilitation

The rehabilitation will be recorded but left entirely to the discretion of the treating surgeon, as the type of injury will vary between patients.

#### Follow-up

Baseline, standardised radiographs will be copied onto CD from the hospital PACs (archiving) system. Copies of the baseline clinical report forms and CD will be delivered to the trial coordinating centre.

The research associate will make a record of any early complications at the routine 6-week follow-up appointment and take a photograph of the wound. This data will be returned to the trial coordinating centre, together with a copy of the routine 6-week follow-up radiograph. The number and timing of any subsequent follow-up appointments will be at the discretion of the treating surgeon. All patients will be reviewed at 12 months as per routine practice after this type of injury. Details of any late complications and copies of the 12-month radiographs will be sent to the trial coordinating centre.

The functional outcome data will be collected using questionnaires at 3, 6, 9 and 12 months postoperatively (see table 2). In addition to the DRI, the patients will be asked to fill out the EuroQol and SF-12 questionnaires, and a complications/further surgical interventions and health economics questionnaire. The 3, 6 and 9 months postoperative questionnaires will be sent to the patients by post, a process done centrally by a data clerk at the Warwick CTU. All of the outcome questionnaires can be completed over the phone if postal copies are not returned. Patients will be asked to complete their 12 months postoperative questionnaire during their routine follow-up appointment 1-year postoperation.

**Table 2 BMJOPEN2015009087TB2:** Follow-up measures

Time point	Data collection
Baseline	DRI and SF-12 preinjury, EQ-5D preinjury and contemporary, routine radiographs of leg wound(s)
6 weeks	Complication records, radiographs, operative record, photograph of leg wound(s)
3 months	DRI, EQ-5D, SF-12 record of complications/rehabilitation or other interventions, and economics questionnaire
6 months	DRI, EQ-5D, SF-12 record of complications/rehabilitation or other interventions, and economics questionnaire
9 months	DRI, EQ-5D, SF-12 record of complications/rehabilitation or other interventions, and economics questionnaire
12 months	DRI, EQ-5D, SF-12 record of complications/rehabilitation or other interventions, and economics questionnaire, radiographs

DRI, Disability Rating Index.

